## 59 I. STUDY OBJECTIVES

60 Annually 313 million surgical procedures are performed worldwide. However, few  
61 studies have explored the anesthesia emergence position in patients with general  
62 anesthesia. We aimed to investigate the efficacy and safety of different degrees of  
63 semi-recumbent position for anesthesia emergence.

64

65

66

67

68

69

70

71

72

73

74

75

76

77

78

79

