#### **E. Randomization and Blinding**

Randomization was performed using a computer-generated random numbers table with a block size of 6 and a 1:1:1 ratio after stratification according to the type of surgery and age. Allocation was sequentially numbered and sealed in opaque

---

envelopes by the corresponding author. The anesthesiologists opened the envelopes 10 min before the emergence procedure. Because of the nature of the intervention, full blinding of all study personnel was not feasible. However, to minimize bias, we attempted to blind patients, practitioners (where possible), research assistants, and data analysts. It was not feasible to blind the PACU anesthesiologists and nurses. To achieve patient blinding, during the informed consent process, we described all interventions as anesthesia emergence positions, and we explained that depending on group allocation, patients may receive different emergence positions during anesthesia emergence. We additionally performed an analysis of blinding success of patients using Bang's Blinding Index.

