### *ii. Perioperative management*

Continuous monitoring was conducted for all patients through the use of electrocardiograms, noninvasive blood pressure measurements, bispectral index (BIS) electrodes (monitoring depth of anaesthesia), pulse oxygen saturation (SpO2) measurements, and end-tidal CO2 (ETCO2) measurements. Sufentanil 0.5 µg/kg, propofol 1.5 to 2.0 mg/kg, and rocuronium 0.8 mg/kg were used for anaesthesia induction. Anaesthesia was maintained with remifentanyl 0.1 to 0.3 µg/kg/min and propofol 4 to 12 mg/kg/h. After intubation, an arterial catheter was placed in the radial artery for blood gas sampling and invasive blood pressure monitoring. BIS value between 40 and 60 were maintained by adjusting the dose of propofol. The respiratory rate was initially set at 12 breaths/min and further adjusted to maintain end-tidal carbon dioxide pressure between 35 and 45 mmHg. Mechanical ventilation was maintained in a volume-controlled mode. Lung protective ventilation was used during surgery (the combination of tidal volume 8 ml/kg predicted body weight or lower and PEEP 5 cm H2O or higher, with a recruitment manoeuvre, fraction of inspired oxygen 60%) in all patients. Mean arterial pressure was maintained within ±20% of the baseline. Hypotension was treated with phenylephrine 40 µg, ephedrine 5 mg, or a fluid bolus; episodes of hypertension were managed by increasing the propofol or remifentanyl infusion rate. If the heart rate was less than 40/min, atropine 0.5 mg (i.v.)

was administered. The type and volume of fluid infusion were determined by the anesthesiologist. Rocuronium was continuously infused at a rate of 0.3 to 0.8 mg/kg/h and stopped approximately 40 minutes before the end of surgery. Postoperative patient-controlled intravenous analgesia (PCIA) was administered (sufentanil 2 µg/kg, tropisetron 10 mg, 0.9% saline diluted, the total volume of the solution is 100 ml.) and was set at 0.5 ml/press with a 15 minutes locking time. Pain scores (Visual Analogue Scale, VAS score) were assessed by nurses in the PACU. Moderate pain (VAS score 4-6) was treated with hydromorphone 0.25 mg, and severe pain (VAS score 7-10) with hydromorphone 0.5 mg, with an aim to reduce pain scores to less than 4. Once the Aldrete score was greater than or equal to 9 out of 10, the patient was discharged back to the ward.

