Prior to extubation, all patients underwent suctioning, with no further stimulation being applied until spontaneous movement was observed. Neuromuscular blockade was reversed using intravenous neostigmine 40 to 60 µg/kg combined with atropine 0.5 mg. Prior to extubation the following criteria had to be met: complete reversal of neuromuscular blockade (a Train-Of-Four ratio greater than 0.90); patient fully awake; and breathing adequately.

After extubation, conventional oxygen therapy (low-flow oxygen ( $\leq 15$  l/min) delivered either by Nasal cannula,  $\text{FiO}_2$  0.35, oxygen flow 3.5 l/min; or Venturi mask,  $\text{FiO}_2$  0.35, oxygen flow 9 l/min) was administered. The recovery nurses did not intervene in the patient's breathing before the onset of hypoxemia, and only when hypoxemia occurred did the recovery nurses correct the hypoxia by encouraging the patient to take deep breaths and increasing the  $\text{FiO}_2$ . In patients who developed  $\text{SpO}_2 < 90\%$  more than 1 minutes, rescue mask ventilation was applied. A decision to re-intubate was made by the anaesthetist in the PACU if the ROX index (defined as the ratio of pulse oximetry/fraction of inspired oxygen to respiratory rate) was less than 4.88. If there was evidence of hemodynamic instability, the intervention was cancelled by the anaesthetist.

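### The only stated trigger for re-intubation, ROX below 4.88, depends so strongly on FiO2 and breathing rate that it can point to a fully saturated patient and miss a slowly breathing hypoxaemic one

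*Protocol*

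**What the plan says.** All the care steps are in the protocol, section III.I, part ii (Perioperative management).

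- **Oxygen after extubation.** Conventional low-flow oxygen at FiO2 0.35, by nasal cannula or Venturi mask ("oxygen flow 3.5 l/min; or Venturi mask").
- **At hypoxaemia.** Nurses respond by "encouraging the patient to take deep breaths and increasing the" FiO2. No level is given for the increase.
- **SpO2 below 90% for more than 1 minute.** Rescue mask ventilation.
- **Re-intubation.** "A decision to re-intubate was made by the anaesthetist in the PACU if the ROX index" is less than 4.88. The index is defined there as SpO2/FiO2 divided by respiratory rate. This is the only re-intubation criterion stated. The sentence on haemodynamic instability cancels the intervention and does not govern re-intubation.

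Reference 16, cited for the index, has a title about predicting the outcome of nasal high-flow therapy. Section III.J makes re-intubation one of the two components of the secondary outcome airway rescue; mask ventilation is the other. Section I gives the aim: "We aimed to investigate the efficacy and safety of different degrees of" semi-recumbent position. Section III.E says "It was not feasible to blind the PACU anesthesiologists and nurses".

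**The concern.** Safety is part of the stated aim, and re-intubation is the most serious airway event the protocol names. A written trigger for it should identify patients who are failing and leave alone those who are not.

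The formula makes that doubtful in two ways. FiO2 is a divisor, so raising oxygen lowers the index even if the patient is otherwise unchanged, and the protocol does not say at what FiO2 the index is read. Respiratory rate is also a divisor, so slow breathing raises the index and moves the patient away from the trigger. Slow breathing is one way a patient given opioids after anaesthesia can fail, and PACU patients here may receive hydromorphone ("severe pain (VAS score 7-10) with hydromorphone 0.5 mg").

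At stake is whether the stated rule describes a sensible bedside decision, and whether it standardises one component of a secondary outcome.

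**Working it through.** **Inputs**

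- Trigger: ROX < 4.88, with ROX = (SpO2/FiO2)/RR (section III.I.ii). SpO2 is taken in percent. As a fraction, 0.90/0.35/12 = 0.21, and the trigger would be met almost always, so that reading is not plausible.
- FiO2 0.35: the stated starting level. After escalation no level is stated, so the range up to the physical maximum of 1.0 is shown.
- SpO2 90%: the protocol's own limit for mask ventilation.
- RR 12/min: the protocol gives this only as a ventilator setting during surgery ("The respiratory rate was initially set at 12 breaths/min"). As a spontaneous PACU rate it is an illustration, so 8 and 20/min are shown too.

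The value 4.88 is a cited cut-off with no inputs in the document, so there is no figure of the plan's own to reproduce.

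**Step 1. Breathing rate needed to meet the trigger**

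RR > SpO2/(FiO2 × 4.88)

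| FiO2 | SpO2 90% | SpO2 80% |
|---|---|---|
| 0.35 | 52.7 | 46.8 |
| 0.40 | 46.1 | 41.0 |
| 0.50 | 36.9 | 32.8 |
| 0.60 | 30.7 | 27.3 |
| 0.80 | 23.1 | 20.5 |
| 1.0 | 18.4 | 16.4 |

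In whole breaths at SpO2 90%, that is 53/min at the starting FiO2 (ROX 4.95 at 52/min, 4.85 at 53/min) and 19/min at FiO2 1.0. Going from 0.35 to 1.0 divides the index by 1.0/0.35 = 2.86 at unchanged SpO2 and rate.

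**Step 2. SpO2 below which the trigger is met**

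SpO2 < 4.88 × FiO2 × RR

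| RR | FiO2 0.35 | FiO2 0.60 | FiO2 1.0 |
|---|---|---|---|
| 8/min | 13.7% | 23.4% | 39.0% |
| 12/min | 20.5% | 35.1% | 58.6% |
| 20/min | 34.2% | 58.6% | 97.6% |

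FiO2 cannot exceed 1.0, so the last column is the most sensitive the trigger can be. At 12/min no FiO2 lets it flag SpO2 60%.

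**Step 3. Ordering of two patients, both at FiO2 1.0**

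- SpO2 100%, 21/min: 100/1.0/21 = 4.76. Trigger met.
- SpO2 60%, 12/min: 60/1.0/12 = 5.00. Trigger not met.

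The index ranks the saturated patient as the one to re-intubate.

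**The case against.** The arithmetic is not in dispute; its reach is. Five objections have weight.

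1. **The starting FiO2 has been left behind by then.** FiO2 is raised at hypoxaemia and mask ventilation follows, so re-intubation is considered on higher oxygen. A reader might infer from 53/min that the trigger is out of reach in this trial. The documents do not support that: at FiO2 1.0 about 19/min suffices. This objection stands, and the two figures must be read together.

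2. **The text says if, not only if.** A reader might infer that the protocol forbids re-intubating a slowly breathing patient, or leaves that patient without help. It does neither. The decision lies with the anaesthetist, and SpO2 below 90% for more than 1 minute leads to mask ventilation whatever the index. What remains is the next step: once mask ventilation fails, the only written trigger is one that slow breathing hides.

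3. **Slow breathing is only thinly supported.** Extubation requires a train-of-four ratio above 0.90, full wakefulness and adequate breathing. "Postoperative patient-controlled intravenous analgesia (PCIA) was administered", but the dose is small: 2 µg/kg in 100 ml at 0.5 ml per press is 0.01 µg/kg, or 1/50 of the 0.5 µg/kg induction dose. With a 15-minute lockout the maximum is 0.04 µg/kg/h. Patient-controlled sufentanil is therefore weak support. Hydromorphone remains a possible cause.

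4. **The consequence for the trial is small.** Hypoxaemic patients who have been mask-ventilated already count as airway rescue. Because unblinded staff choose the FiO2, a reader might infer bias between arms, but nothing in the protocol shows any. Nor can one infer that rate and FiO2 are unavailable: section III.J describes continuous monitoring with review of the monitor database, and applying the index requires both values.

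5. **The high-flow mismatch rests on a title.** It shows that the cited setting differs. It does not show how badly 4.88 carries over, so the case rests on the formula.

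**Conclusion.** The point holds in a narrow form. The only re-intubation trigger the protocol states can order patients the wrong way round: at FiO2 1.0 it is met at SpO2 100% and 21/min and not met at SpO2 60% and 12/min. The rate it requires at SpO2 90% runs from about 53/min to about 19/min, depending on an FiO2 the protocol leaves open.

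This rests on the protocol's own definition with SpO2 in percent, on FiO2 1.0 as the upper bound, and on 12/min as an illustrative rate. The direction does not depend on the illustration, because rate is in the denominator.

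The point concerns the wording of a safety rule and the re-intubation part of one secondary outcome. The primary outcome and the sample size are unaffected. The protocol gives no expected number of re-intubations, so the number of patients affected cannot be computed, and harm to patients is not shown. It is a minor point, worth acting on because the correction is cheap.

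**What to change.** Replace the re-intubation sentence in section III.I.ii with:

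*Re-intubation is decided by the PACU anaesthetist; apnoea, inadequate breathing, or SpO2 <90% persisting despite mask ventilation are grounds in themselves; ROX <4.88 may inform the decision but is neither required nor sufficient.*

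This adds no new numerical cut-off, since 90% is already the protocol's limit for mask ventilation. It needs no device and leaves the primary outcome unchanged.

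The cost is that the decision becomes openly a clinical judgement by staff who know the patient's position, and inadequate breathing is not defined numerically. The protocol already relies on adequacy of breathing, undefined, as an extubation criterion, and already leaves re-intubation to the anaesthetist. The change therefore makes an existing judgement explicit, but it does give up a single objective number.

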## **J. Measurements and Endpoints**

The primary outcome was the incidence of postoperative hypoxaemia in the PACU (defined as  $\text{SpO}_2 < 90\%$  for more than 10 seconds or  $\text{PaO}_2:\text{FiO}_2$  ratio below 300 mmHg). We also recorded the incidence of severe hypoxaemia ( $\text{SpO}_2 < 85\%$  for more than 10 seconds) and the time to first episode of hypoxaemia. Patients were continuously monitored real-time vital signs in the PACU using a Mindray BeneVision N15 monitor (Shenzhen Mindray Bio-Medical Electronics Co., Ltd.). In this study, data collection was performed by one-on-one researchers in the PACU, review of the monitor's database by the data collector when the patient leaving the PACU. To avoid pulse oximeter probe dislodging the finger or having it only partially on the finger, we used disposable finger probes that stick to the finger like a Band-Aid for continuous monitoring (Disposable  $\text{SpO}_2$  Sensor, Shenzhen Mindray Bio-Medical Electronics Co., Ltd.).

The secondary outcomes included:

airway rescue (defined as the need for mask noninvasive positive pressure ventilation, or re-intubation);

respiratory symptoms (coughing);

extubation time (defined as the time from end of surgery to extubation);

respiratory comfort (before leaving PACU, graded using a numerical rating scale, ranging from 0 to 10, higher score means more comfort);

duration of stay in the PACU;

wound pain (VAS score measured at rest, while coughing at 5 and 30 minutes after extubation, before leaving PACU, and 24 hours post operation);

and position-related adverse events (hypotension, arrhythmia, and some other adverse events).

The patient's vital signs (heart rate and mean arterial pressure) were recorded at six time points: (1) the beginning of surgery (T0); (2) the end of surgery (T1); (3) immediately after adjusting position (T2); (4) immediately prior to extubation (T3); (5) 1 min after extubation (T4); (6) when leaving the PACU (T5).

Dynamic lung compliance ( $\text{C}_{\text{dyn}}$ ) and driving pressure ( $\Delta P$ ) were also recorded at

---

320 three time points: (1) when stitching; (2) 5 minutes after adjusting position; and (3)  
321 before extubation.

322 Arterial blood gas analysis was performed at three time points: (1) when stitching; (2)  
323 5 minutes after adjusting position; (3) 5 minutes post-extubation.

324

---

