#### **G. Statistical Analysis**

Continuous variables were presented as mean (SD) or median (interquartile range, [IQR]), depending on whether the data was distributed normally or not. Categorical variables were presented as a number (percentage). The normal distribution of data was evaluated using the Shapiro–Wilk test, and the Levene method was used to test the homogeneity of variance. Differences in repeated measures variables were analysed by repeated-measures analysis of variance. Continuous outcomes were

analysed with one-way analysis of variance (ANOVA) or Kruskal-Wallis test. Categorical variables were tested using  $\chi^2$  test or Fisher's exact test. The primary analyses were performed according to the intention-to-treat (ITT) principle. Modified ITT (mITT) and per-protocol (PP) analyses were also performed as sensitivity analyses for the primary outcome. Results of primary and secondary outcomes were reported as relative risk (RR) or between-group difference with 95 % CI, the absolute risk reduction (ARR) and Number needed to Treat (NNT) were also calculated, with 95% CI. Kaplan-Meier curves were used for the time to first experience hypoxaemia. When an overall intervention effect was detected ( $P < 0.05$ ), the Bonferroni correction for multiple pairwise comparisons would be performed. To handle missing data, multiple imputations by chained equations was used, assuming missing data are missing at random. Imputation for continuous data was performed by predictive mean matching, logistic regression for binary variables. The number of imputations was 5. Convergence of the multiple imputation algorithm and the results of the imputation were checked. Imputations were performed with the R MICE package (J Stat Software. 2011;45(3):1–67.). Analyses were then performed on each of the imputed data sets and pooled according to Rubin's rules. As a post hoc sensitivity analysis, we used a logistic regression model simultaneously entering: age, BMI, current smoking status, chronic pain needing opioids, ARISCAT score (Assess Respiratory Risk in Surgical Patients in Catalonia), CCI (Charlson Comorbidity Index), surgery time, intraoperative opioid consumption, and the use of a nasogastric tube. R version 4.1.1 was used for statistical analysis, and analysis items with 2-sided  $P < 0.05$  were considered statistically significant.

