## H. Intervention

At the end of operation, patients were transferred from operating table to transfer bed, and their positions were adjusted according to the groups.

supine position group (group S): Patients were placed in supine position from the end of surgery to leaving PACU.

15-degree semi-recumbent position group (group F): Patients were placed in 15-

---

degree semi-recumbent position from the end of surgery to leaving PACU.

30-degree semi-recumbent position group (group T): Patients were placed in 30-degree semi-recumbent position from the end of surgery to leaving PACU.

The inclination angle was set precisely by an inclinometer (GeeLii 55157, Shanghai GeeLii International Trade Co., China)

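### The primary outcome does not separate new from carried-over PaO2:FiO2 deficits, and no listed primary-outcome analysis uses the blood gas taken before positioning

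*Protocol*

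**What the plan says.** Section III.J defines the main endpoint: "The primary outcome was the incidence of postoperative hypoxaemia in the PACU". An event is either SpO2 under 90% lasting more than 10 seconds or a PaO2:FiO2 ratio under 300 mmHg. Nothing requires the low ratio to be new.

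The same section schedules the gases: "Arterial blood gas analysis was performed at three time points: (1) when stitching; (2" and (3) follow 5 minutes after positioning and 5 minutes after extubation. Section III.H places the intervention after stitching: "At the end of operation, patients were transferred from operating table to transfer bed, and their positions were adjusted according to the groups". The first gas therefore precedes the tilt in every arm.

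Section III.C excludes underlying lung disease and respiratory failure but sets no oxygenation threshold before positioning.

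Section III.G tests categorical outcomes with a chi-square or Fisher test, takes ITT as primary, and adds mITT and PP as sensitivity analyses. It then describes a post hoc analysis: "we used a logistic regression model simultaneously entering: age, BMI, current smoking status, chronic pain needing opioids, ARISCAT score", followed by CCI, surgery time, intraoperative opioid consumption and nasogastric tube. That makes nine covariates. The stitching PaO2:FiO2 is not among them.

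**The concern.** Take two hypothetical patients. One has a ratio of 270 when stitching and 290 after extubation; the other falls from 450 to 290. The first improved under the allocated position and the second deteriorated, yet both are the same primary event. The same problem touches the planned Kaplan-Meier curves for time to first hypoxaemia, because a deficit present before the tilt has no onset to time.

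The protocol already collects the value that would tell these patients apart. It is also an earlier measurement of one of the two components of the outcome, and so a natural candidate for the most prognostic covariate available. Leaving it out while adjusting for nine others may forgo precision. It also leaves open whether position prevented new hypoxaemia, resolved an existing deficit, or did neither in patients who arrived with one.

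**Working it through.** **1. The protocol's own sample size.** Inputs from section III.F: 46% supine, 34% combined semi-recumbent, 2:1 ratio, two-sided 5%, 80% power, continuity correction.

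- Pooled rate: (0.46 + 2 × 0.34)/3 = 0.38.
- Uncorrected supine n = [1.960 × √(0.38 × 0.62 × 1.5) + 0.842 × √(0.46 × 0.54 + 0.34 × 0.66/2)]² / 0.12² = 193.8, rounded up to 194 (582 in total).
- With continuity correction: (193.8/4) × [1 + √(1 + 2 × 3/(2 × 193.8 × 0.12))]² = 206.1, rounded up to 207. The total is 207 + 414 = 621, against 620 stated.
- Power at 620 is 80.1% with the correction and 82.4% without.

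The stated figure reproduces. If the pilot used the same composite definition, any carried-over deficits are already inside 46% and 34%, and planned power is unchanged. The protocol does not state the pilot's definition.

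**2. How many events could be carried over.** The protocol gives no distribution of PaO2:FiO2 at stitching, so both inputs are assumptions. Suppose stitching and post-extubation values are bivariate normal and every supine event arises through PaO2:FiO2. The share of supine events already below 300 is then P(both low)/0.46.

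| Assumed share of patients below 300 when stitching | Share of supine events, correlation 0.4 to 0.7 |
|---|---|
| 5% to 10% | 9% to 20% |
| 20% to 40% | 30% to 66% |

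The answer runs from minor to dominant, and the protocol cannot narrow it.

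**3. What adjustment could gain.** I simulated 206 supine and 414 semi-recumbent patients at 46% and 34%, with 6,000 trials per cell. A latent normal outcome has correlation r with the stitching value. The unadjusted analysis is the chi-square test; the adjusted one is a likelihood-ratio test in a logistic model containing the stitching value. For the mixed case, an SpO2 component independent of the stitching gas has the same probability as the PaO2:FiO2 component: 1 − √0.54 = 0.265 each in the supine arm and 1 − √0.66 = 0.188 each in the others. The combined rates are therefore still 46% and 34%.

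| r | All events via PaO2:FiO2: unadjusted, adjusted | Half via independent SpO2: unadjusted, adjusted |
|---|---|---|
| 0 | 0.824, 0.821 | 0.826, 0.822 |
| 0.3 | 0.820, 0.836 | 0.830, 0.830 |
| 0.4 | 0.827, 0.857 | 0.815, 0.828 |
| 0.5 | 0.832, 0.883 | 0.828, 0.850 |
| 0.6 | 0.822, 0.909 | 0.832, 0.859 |

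The standard error of each power is about √(0.83 × 0.17/6000) = 0.005. For r from 0.3 to 0.6 the gain is about 2 to 9 points in the first case. In the second it is about 0 to 3, or up to about 4 allowing for simulation error and other ways of mixing the components. If three quarters of events come from SpO2, the gain is about 0 to 1 point. At r = 0 the loss is within simulation error.

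**The case against.** The strongest reply has four parts.

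- **An unadjusted test in a randomised trial is valid.** This stands. The outcome as defined is compared without bias, and the power check shows no shortfall against plan.
- **Resolving a deficit is part of the treatment effect.** This also stands. The outcome is hypoxaemia in the PACU, and a position that lifts a patient from below to above 300 mmHg has done something useful. It is wrong to treat carried-over deficits as beyond the reach of position.
- **The stitching gas is not like-for-like.** Section III.I prescribes intraoperative ventilation with PEEP of at least 5 cm H2O, a recruitment manoeuvre and FiO2 60%; after extubation the patient breathes FiO2 0.35. Section II.B itself notes that the oxygenation benefit of recruitment and PEEP fades quickly at emergence. This weakens 300 mmHg at stitching as a filter for new onset. It does not undermine continuous adjustment, which needs correlation, not equal scales. Envelopes are opened 10 minutes before emergence, so some stitching gases may follow disclosure of the allocation, but they still precede the tilt.
- **Covariate choice belongs in the SAP, which is not at hand.** This is true of covariates in general. Here, however, the protocol itself names the test, the sensitivity analyses and a complete covariate list, so the omission is a choice it has made. A separate SAP could still repair it.

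**Conclusion.** The point holds as a missed opportunity in analysis and interpretation. The definition mixes new and carried-over PaO2:FiO2 deficits, and none of the listed primary-outcome analyses uses the pre-positioning value that is already scheduled. Under the assumptions above, the forgone power lies between nothing and about 9 points, depending on a correlation and an event mix that the protocol does not give.

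Three stronger readings are tempting but unsupported.

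- **Carried-over deficits do dilute the effect.** That requires a material share of patients to be below 300 when stitching and to stay there whatever the position. The protocol shows neither.
- **The trial is underpowered for this reason.** This would follow only if the pilot's 46% and 34% counted new events alone and a further share q were events in every arm. With q = 10%, for example, the rates become 0.10 + 0.90 × 0.46 = 51.4% and 0.10 + 0.90 × 0.34 = 40.6%, and continuity-corrected power at 620 falls to 69%. It would be 75% at q = 5%, 58% at 20% and 48% at 30%. Nothing indicates that the pilot was defined that way.
- **Patients at 300 mmHg or above when stitching give the true incidence of new hypoxaemia.** They do not, because the two gases are taken under different ventilatory conditions.

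**What to change.** - Prespecify an adjusted analysis of the primary outcome with stitching PaO2:FiO2 as a continuous covariate. At the least, add it to the existing logistic model.
- Report the RR and risk difference from that model by standardisation, so that they sit beside the unadjusted RR and ARR already planned.
- Handle missing stitching gases in the multiple imputation already described in section III.G.
- Optionally, add an analysis restricted to patients whose stitching ratio was at least 300 mmHg, labelled supportive, with the difference in ventilatory conditions stated.
- State which hypoxaemia definition the pilot used, so that the reader can see whether 46% and 34% already include carried-over deficits.

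The cost is wording and one covariate. The gas is already scheduled, so no change to conduct or sample size is needed, and the simulation shows essentially no loss if the covariate proves uninformative. If outcome data have already been seen, the adjusted analysis should be labelled post hoc, as the present logistic model is.

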#### IV. DATE AND SAFETY MONITORING

Clinical research will formulate a corresponding data safety monitoring plan according to the size of the risk. In the implementation stage of clinical research, record all adverse events in detail, handle and track them properly until they are properly resolved or the condition is stable, and report serious adverse events and unexpected events to the ethics committee, competent authorities and drug regulatory authorities in a timely manner as required; The principal investigator will periodically conduct a cumulative review of all adverse events, and if necessary, hold an investigator meeting to assess the risks and benefits of the study; We will arrange independent data monitors to monitor the research data, and high-risk studies will establish an independent data safety monitoring committee to monitor the accumulated safety data and efficacy data to make a decision on whether to continue the study.

---

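### The safety outcome is worded as "position-related" events, an undefined and open-ended restriction that could let attribution, rather than event rates, drive the comparison between arms

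*Protocol*

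**What the plan says.** The Study Objectives (protocol, section I) set out to "investigate the efficacy and safety of different degrees of" semi-recumbent position, so safety is an aim alongside efficacy. The only outcome labelled as safety is a secondary one in section J (Measurements and Endpoints): "position-related adverse events (hypotension, arrhythmia, and some other adverse events". Two events are named and the rest is left open. The section does not say how an event comes to count as position-related, or who decides.

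On knowledge of the arm, section E (Randomization and Blinding) states "It was not feasible to blind the PACU anesthesiologists and nurses", but also "we attempted to blind patients, practitioners (where possible), research assistants, and data analysts". Section J adds that "data collection was performed by one-on-one researchers in the PACU". Under section H (Intervention) each arm keeps its position throughout; for the control arm, "Patients were placed in supine position from the end of surgery to leaving PACU".

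Two further provisions bear on the point. Section IV (safety monitoring) requires the team to "record all adverse events in detail, handle and track them properly until they are properly resolved or the condition is stable". Section I.ii (Perioperative management) provides that, on evidence of haemodynamic instability, "the intervention was cancelled by the anaesthetist".

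**The concern.** Randomisation protects a comparison of all events that occur in each arm. It does not protect a comparison of events that have first passed a causal judgement, if that judgement can depend on the arm. Section C (Preliminary Studies) describes supine as the position most anaesthesiologists prefer. The same fall in pressure could therefore be put down to the tilt in a semi-recumbent patient and to something else in a supine one. The opposite tendency is also possible.

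At stake is the safety half of the objective. A filter of this kind could show a harm of tilting that does not exist, or hide one that does. The open category adds to the problem, because unlisted events cannot be counted until someone decides which of them belong.

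**Working it through.** **1. Is there a figure in the plan to reproduce?** Not for this outcome. The only sample-size calculation is for hypoxaemia (section F: 46% vs 34%, 2:1, two-sided 5%, 80% power, continuity correction). It reproduces at 207 + 414 = 621 against the stated 620, and it does not bear on safety. The one input taken from it is the planned recruitment: 700 / 3 ≈ 233 per arm.

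**2. Two readings of the outcome.**
- *Label:* hypotension, arrhythmia and the rest are counted whenever they occur. Counted rate = true rate, and there is no bias.
- *Filter:* an event counts only if attributed to position. Counted rate in arm j: q_j = p_j × a_j, where p_j is the true rate and a_j the share attributed.

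Under the filter the apparent relative risk is (p_tilt/p_supine) × (a_tilt/a_supine). Equal shares leave it unchanged; only a difference in shares distorts it.

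**3. Creating a difference.** All p and a values are assumptions; none is in the protocol. The true rate is the same in every arm. The test is the one in section G, an overall chi-square across three groups (2 degrees of freedom, 5% level), with 233 per arm and both tilted arms sharing one attribution share.

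| True rate | Shares, supine / tilted | Counted rates | Apparent RR | Falsely significant |
|---|---|---|---|---|
| 5% | 40% / 60% | 2% / 3% | 1.5 | about 9% |
| 10% | 40% / 60% | 4% / 6% | 1.5 | about 14–15% |
| 20% | 40% / 60% | 8% / 12% | 1.5 | about 29% |
| 5% | 20% / 80% | 1% / 4% | 4.0 | about 53% |
| 10% | 20% / 80% | 2% / 8% | 4.0 | about 89% |
| 20% | 20% / 80% | 4% / 16% | 4.0 | about 100% |
| any of these | equal | equal | 1.0 | 5% |

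The last column comes from simulation. As a hand check, the noncentrality is λ = n Σ(q_j − q̄)² / [q̄(1 − q̄)].
- 10%, 40/60: q̄ = 0.0533, and λ = 233 × 0.000267 / 0.0505 ≈ 1.23, which gives about 15%.
- 10%, 20/80: q̄ = 0.06, and λ = 233 × 0.0024 / 0.0564 ≈ 9.9, which gives about 81%. The approximation is rough at a counted rate of 2%; simulation gives 89%.

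**4. Masking a difference.** Suppose the true rates are 10% supine and 20% in both tilted arms. With every event counted, the three-arm test is significant in about 89% of simulated trials. If 90% of supine and 45% of tilted events are attributed, the counted rates are 0.10 × 0.90 = 9% and 0.20 × 0.45 = 9%. The apparent RR is 1.0 and the chance of significance falls to 5%.

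**5. Does the text settle the reading?** No. Section J supports either. Section IV ensures that all events are recorded, but it sits under monitoring and does not make them an outcome compared by arm.

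**The case against.** The strongest reply is that the protocol describes no attribution step. The parenthesis lists types of event, and the phrase reads naturally as a heading for events that position might cause. A reader might infer that the outcome counts only events which unblinded staff have judged, case by case, to be due to position. The document does not support that. It mentions no causality assessment and no assessor. The sentence on unblinded anaesthesiologists and nurses does not make them the judges, and blinding of research assistants was attempted. This stands, and it limits the point to ambiguous wording. It does not remove the point, because the open category needs a decision under either reading, and anyone collecting data at the bedside could see the bed angle.

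Second, safety does not rest on this item alone. Heart rate and mean arterial pressure are recorded at six times (T0 to T5) and need no attribution. This also stands, but spot readings can miss episodes between them and do not cover arrhythmia or other events.

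Third, numeric thresholds and event lists are often left to the statistical analysis plan, which is not at hand. Agreed: the missing threshold is not the complaint. The complaint is that the protocol itself fixes the outcome with a restricting word whose effect is unclear.

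Fourth, the magnitudes are hypothetical. That is so, and with milder shares they are modest.

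**Conclusion.** The concern holds in a limited form. The safety outcome carries an undefined restriction and an open category, without a relatedness rule or blinded assessor, in a setting where the position is visible. Applied as a filter with shares that differ by arm, it can bias the comparison in either direction. Read as a label, it causes no such bias.

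The size is illustrative only: at a 10% true rate, false significance of about 14 to 15% (40% vs 60%) to 89% (20% vs 80%), against a nominal 5%. These figures rest on assumed event rates and shares, equal shares in the two tilted arms, 233 patients per arm and the overall three-group test. They do not show that the trial's safety result is biased. The primary outcome and the sample size are unaffected.

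**What to change.** Drop the position-related restriction. Compare all hypotension, arrhythmia and other adverse events, from position adjustment to leaving the PACU, by randomised arm and regardless of attribution. Use the adverse event records that section IV already requires. Apply one objective outcome definition of hypotension alike in all arms to the monitor data, not to the six spot readings alone. This concerns counting only and changes no treatment rule. Keep any attribution as a descriptive column.

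Report cancellations for haemodynamic instability descriptively by assigned arm. They are informative about tolerability, but they are a discretionary act by unblinded staff and should not be counted as outcome events.

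The cost is the wording of one secondary outcome and one table, assuming that the monitor database holds the pressures and that the records were kept as section IV requires. The small downside is that background events unrelated to position dilute the contrast slightly.
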